#### Recruitment and informed consent

Participants will be recruited both offline and online, by posters and flyers of the website “Feel the ViBe” spread amongst stakeholders in the field, general websites and social media to reach as many participants as possible. In this target group, internet literacy is assumed.

According to the principles of Dutch law, for participants age 12 to 16 years old, both parents (or guardians) must consent in addition to the minor him/herself. However, in cases of family violence, informing the abusive partner can be potentially dangerous, for both the abused parent and the adolescent exposed to the violence, and safety cannot be ensured. Therefore, in these cases we ask informed consent from the abused parent, being the mother in most cases, only.

Participants register themselves by sending an email to the community manager through the contact form online. In this early phase, inquiring participants about the type and severity of the violence would enlarge the threshold for participation. We therefore choose to consider every potential participant eligible as target group. If participants have read the patient information letter, available on the homepage, and have no further questions, they are eligible to participate and will receive a login name and password. On their first login, participants have to give informed consent electronically. If applicable, participants are requested to provide contact information of their parent(s), who then receive a unique code and a link to give consent as well.

The intervention is internet-based without face-to-face components. This means that participants are quasi-anonymous for each other. Having multiple identities is being prevented by making the registration a manual process, including a IP-address check and e-mail contact, and the informed consent process.

### Settings

Participants can access “Feel the ViBe” from any computer, needing only their login name and password. All outcomes will be self-assessed through online questionnaires.

### Development of the intervention

Before starting the internet-based self-support method we conducted a literature research, consulted experts in the field and identified existing healthcare services available for adolescents exposed to family violence. We then identified three aims for a first version of the internet-based method “Feel the ViBe (Violence Beaten)”:

1. To offer peer support.

2. To offer information on family violence in broad sense, including information on dating violence and sexual and reproductive health.

3. To lower the threshold to existing healthcare by supplying information about healthcare services.

We set up criteria for the company building the internet-based self-support method, being:

1. Experience in building psychosocial interventions

2. Experience in building internet-based methods for adolescents

3. Employing a medical ICT specialist

4. Being able to comply to the safety and privacy rules for websites processing patient details.

5. Having all the necessary facilities, without having to hire consultants.

Two companies fitted these requirements, from which we selected the company that could provide personal support to the researchers daily, being “Re:publik”.

Based on expert opinions, literature, and in close collaboration with the medical ICT specialist from “Re:publik” we identified key elements and requirements of the internet-based method, divided in content available for everyone visiting “Feel the ViBe” and content for participants only. While a basic version of “Feel the ViBe” was being built, the researchers recruited GP’s to identify adolescents exposed to family violence who were not in an immediate need for professional care, and asked them to take part in a semi-structured interview about online support, reproductive and sexual health and wishes, needs, and expectations for general healthcare. Themes emerging from these interviews were used to formulate important features and subjects for the website and were added to the basic version of “Feel the ViBe”.

To improve the intervention further, we asked all participants who took part in the semi-structured interview to visit the website extensively as if they were actively searching for help at that time and comment on the website using a Web Evaluation Questionnaire (WEQ) about the goals, content and lay-out. Their were used to make final improvements on “Feel the ViBe”. This led to the intervention as described below.

### Intervention

“Feel the ViBe” is an internet-based intervention without face-to-face elements. “Feel the ViBe” is based on the theory that self-help, by means of peer-support and information, is an effective way of healthcare for the majority of the target group, while a minority will need further, face-to-face, help. The intervention is available online via http://www.feel-the-vibe.nl and consists of several elements, being amongst others a forum, a chat function, information, and a “ask the expert” function (Table 1). More information can be obtained by contacting the corresponding author. During the RCT the intervention will be ‘frozen’: no changes will be made to the intervention, except for changes due to unexpected events, such as bug fixes. These and other unexpected events, such as system downtimes, will be registered.

**Table 1 T1:** "Feel the ViBe" elements

**Element**	**Extra information**	**Restrictions**
General information on exposure to family violence	Information by age (under-twelve, 12–17, 18–25 and parents) and by subject.	No restrictions
Research information & disclaimer	Information for participants and parents about research, safety and privacy.	No restrictions
Information on sponsoring	Homepage, bottom left.	No restrictions
Contact page	Option to register or ask questions to the community manager or researchers.	No restrictions
News page	Twitter newsfeed included. The news page states important information for participants such as major bug fixes, changes in content and scheduled maintenance.	No restrictions
Emergency exit	A button on every page directing participants to http://www.google.nl.	No restrictions
Electronic consent for participants	Consent is necessary to get access to other elements behind login	Available after first login. *Element will be removed after trial.*
Electronic consent for parents	Consent is necessary for participants under 16 years old to get access to other elements behind login	Accessible by e-mail link with a code. *Element will be removed after trial.*
Questionnaires	Measure outcomes and need to be filled out before accessing the elements behind login. Questionnaires will be activated in the personal menu. Questionnaires can be filled out one-by-one. Whenever possible, adaptive questioning is being used to make the burden as low as possible. There is a maximum of 15 questions per page. All items need to be filled out to submit a questionnaire. Participants cannot review their answers.	Available after first login, re-activated after 6,12, 18 and 24 weeks. *Element will no longer be obligated after trial.*
Personal menu	Menu for the participants with overview to all the available elements, access to the participants profile, digital testament, research information and contact information.	Login needed
User profile	The profile contains information on the participant, being: full name, nickname, avatar, sex, age, contact details and contact person. Only the nickname is available for other participants. The participant can choose a theme for the lay-out.	Login needed
Digital testament	The digital testament is required to fill out and lets participants choose how their data must be handled if they stop their participation.	Login needed
Ask the expert	Option to ask questions by e-mail to several experts, including a general practitioner, a sexologist, a psychologist and an expert in the field of family violence. Participants can also contact the community manager for general questions and questions regarding regular healthcare services. Response is given within 72 hours. During the RCT, this is the only available element for participants in the control group.	Login needed & questionnaires finished
Forum	The forum is meant to stimulate peer support. The community manager moderates the forum and stimulates contact. She will not intervene in the conversations except in case of offensive or factually wrong comments.	Login needed & questionnaires finished
Chat	Every two weeks we will offer a chat session for the participants with a specific theme and supported by an expert. Every other week there will be an unguided chat.	Login needed & questionnaires finished
Information	Information will be offered to the participants. Depending on the age in the profile, participants have access to tailored information about partner violence, sexual health, reproductive health, relations and healthcare. Participants are encouraged to discuss topics on the forum.	Login needed & questionnaires finished
Routine Outcome Measurement (ROM)	Directly after login and after logout a popup appears to the participant requesting to state their mood by means of smiley’s. The smiley is optionally visible in the profile as avatar.	Login needed
Facts & Figures	In a twelve-week cycle, participants receive a one-sentence fact of figure about family violence, sexual health, or reproductive health every day on their mobile or by e-mail.	Questionnaires finished

Overview of the elements of the internet-based self-support method “Feel the ViBe”, including restrictions for participants.

“Feel the ViBe” is to be used ad libitum. However, to stimulate participation, participants receive a fact or figure by email or text message every day (Table 1). Elements, such as the guided chat and “facts and figures”, are repeated every twelve weeks. Strictly spoken there is no hard endpoint to the intervention, because “Feel the ViBe” is meant to support participants as long as they need this. However, we decided to link measurements to this twelve week period (Figure 1). Some items are obligatory to fill out to gain access to other features, such as the questionnaires. Restrictions are given in Table 1. “Feel the ViBe” is monitored by a community manager who answers questions, guides the chat, moderates the forum and addresses possible safety issues with participants. To prevent bias, the Community Manager uses a protocol. Every action from the community manager not covered by the protocol will be registered, discussed with the supervising research team, and, if necessary, added to the protocol.

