#### Inclusion criteria

Participants are adolescents in the age of 12–25 years old, exposed to family violence at home. Any adolescent encountering family violence at home, whether this is direct or indirect, is considered to be exposed to family violence.

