#### Secondary outcome measures

•Routine Outcome Measurement (ROM) will be used to follow participants from session to session. On every login, participants will see a pop-up asking them how they would grade their mood at that precise moment on a visual analogue scale using smiley’s. After logging out they will receive a pop-up asking the same question. The scores and differences in scores before and after the session are analyzed to find any direct effects of visiting the website [48].

•An adapted version of the “Seks onder je 25e” (Sex-under-25) questionnaire will be used to measure an increase in knowledge on sexual and reproductive health, including relational health and a decrease of sexual risk taking behaviour. This validated questionnaire is used in a survey in the Netherlands every few years amongst adolescents twelve to twenty-five. In 2011 the questionnaire was filled out online by a representative sample of 10.000 youngsters. It discusses sexual, reproductive and relational health in a broad way handling for example topics as sexual education, ‘the first time’, negative experiences, and contraception. Using this questionnaire will enable us to compare health status of the target group with a population sample. The “Seks onder je 25e” (Sex-under-25) questionnaire is measured at t = 0, t = 2 and t = 4 for both groups [49].

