#### Process evaluation

•The web evaluation questionnaire (WEQ) will contain questions about content, layout, the perceived effectiveness and usefulness of the website, as well as the question to give the website a motivated overall score from 0 to 10, based on their experiences and taking into account their own wishes and needs. The evaluation questionnaire has as goal to identify issues for further improvement of “Feel the ViBe”, to collect possible facilitators and barriers for implementation and to evaluate if the website meets the expectations of the target group. The WEQ is measured twelve weeks after getting access to Feel the ViBe, being t = 2 for the intervention group and t = 4 for the control group.

•“Use” is measured by the collection of quantitative data - being amongst others and duration, visited pages, and visitor numbers - and qualitative data - being forum and chat entries and questions asked to the experts – and is monitored on a continuous base [50,51].

•Demographic variables and data on other (health) care and support received will be collected. At t = 0, participants will also be asked to their expectations, needs and wishes for “Feel the ViBe”.

•After participants have finished all components of the intervention, including all questionnaires, they will be asked if they consent to take part in an interview to discuss in dept their experiences with the intervention.

All questionnaires are provided online and are mandatory to get access to other features. The IES, the SCL-90 and the “Sex-under-25” questionnaire have been administered online before in other studies. Both the general questionnaire and the WEQ have been developed for this trial. Comments and suggestions of test users were incorporated. All the questionnaires have been tested for usability and technical functionality. All responses are being captured automatically.

The primary outcome measures, being the IES and the SCL-90R subscales will be administered four times. This will give us the possibility to determine the optimal duration of the intervention. Participants receive a reminder in their personal menu and via a text message (Figure 1).

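### Every item must be answered before the site opens, sexual-experience items from age 12 included, and no way to decline is described

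*Protocol article*

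**What the plan says.** Table 1 of the protocol article (Intervention) sets two rules for the questionnaires. The first concerns completion: "All items need to be filled out to submit a questionnaire. Participants cannot review their answers". The second concerns access: "Measure outcomes and need to be filled out before accessing the elements behind login".

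The same table lists the restriction "Login needed & questionnaires finished" for Ask the expert, Forum, Chat and Information, and finished questionnaires as the condition for Facts & Figures. The Process evaluation section makes the lock general: "All questionnaires are provided online and are mandatory to get access to other features".

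The Sex-under-25 questionnaire is a secondary outcome. The article describes it as "handling for example topics as sexual education, ‘the first time’, negative experiences, and contraception", and the "questionnaire is measured at t = 0, t = 2 and t = 4 for both groups". On age, the Inclusion criteria read: "Participants are adolescents in the age of 12–25 years old, exposed to family violence at home".

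Three softening provisions also appear. Table 1 says that adaptive questioning is used where possible to limit burden, and that the questionnaires can be completed separately. Ethical and safety issues says that the community manager can be reached by email or telephone even when compulsory parts are unfinished.

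**The concern.** Together, the two rules tie access to the intervention to each single item of a sensitive secondary questionnaire. Adaptive routing can spare a participant the items that do not apply. It is described as a way to reduce burden, not as a way to decline an item that does apply. Someone unwilling to answer such an item has two courses: leave the form unsubmitted and stay outside the gated elements, or enter something to get through.

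Two things are at stake. The first is the quality of the knowledge and risk-behaviour data, on which both secondary objectives rest. An invented answer looks like a true one in the data file, whereas a coded refusal is visible and can be handled as missing. The second is who receives the intervention and who is analysed. The Data analysis section excludes anyone with fewer than five visits to the intervention, so refusing a secondary item can carry over into the primary analysis.

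**Working it through.** The plan gives no figure on this point, so the check is mainly a reading of the rules against each other.

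**1. Does the lock cover the secondary questionnaire?** Yes. The Process evaluation section makes all questionnaires mandatory, and Table 1 has no exemption.

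**2. Is there a stated way to decline?** None is described. The response categories of the adapted questionnaire are not shown, so one may exist.

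**3. What does the lock close, and what stays open?** It closes Ask the expert, Forum, Chat, Information and Facts & Figures. For controls, Ask the expert is the element that Table 1 leaves available during the trial. The public pages, contact page, personal menu, user profile and direct contact with the community manager stay open.

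**4. What happens at each wave?** Table 1 re-activates the questionnaires at 6, 12, 18 and 24 weeks, so t = 2 is week 12 and t = 4 is week 24.

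| Wave | Sex-under-25 given | Effect of one refused item |
|---|---|---|
| t = 0 | yes | Intervention participants cannot open the gated elements; controls cannot open Ask the expert; the five-visit exclusion may follow |
| t = 1 | no | none |
| t = 2 | yes | Controls' access to the intervention is delayed or prevented; the 12-week randomised contrast is already complete |
| t = 3 | no | none |
| t = 4 | yes | No later outcome wave follows |

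**5. Are the primary scales blocked?** No. Questionnaires are submitted one by one and activated in the personal menu, which needs only a login. The IES and SCL-90-R can be submitted at any wave with the sexual-health form unfinished. Later primary data are lost only if the participant disengages.

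**6. Scale, by assumption.** The refusal rate is not in the documents. With the planned 50 per group (100 in all) and an assumed 5% to 10% declining at least one item at a wave, 0.05 × 100 = 5 to 0.10 × 100 = 10 participants are affected, either locked out or giving an unusable answer.

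As an upper bound on lost power, suppose that every such refusal at t = 0 became a loss, spread evenly over the groups. With power = Φ(d√(n/2) − 1.96), two-sided 5%:

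| Loss | n per group | d = 0.7 | d = 0.5 |
|---|---|---|---|
| 0% | 50 | 93.8% | 70.5% |
| 5% | 47.5 | 92.7% | 68.3% |
| 10% | 45 | 91.3% | 66.0% |

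Here 0.7 is the smallest effect among the studies cited in Sample size, and 0.5 is the size which that section calls large. For example, at n = 45 and d = 0.7, 0.7 × √22.5 − 1.96 = 1.36, giving 91.3%. The drop in power is modest, so what matters is selective loss and unidentifiable false answers.

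**The case against.** The strongest reply is that the items are not shown. A decline category would itself be a filled-out item, so the completion rule does not exclude one, and a journal article commonly omits response options. This stands in part: that answers will be false is an inference, and the point falls away if the category exists. The completion rule and the lock are nevertheless stated outright, and the article mentions nothing that relieves them.

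A second reply is that the source questionnaire is validated, has been used online in the same age range, and that the trial's forms were tested by users. This makes heavy refusal less likely. It does not show that participants in this trial could decline an item.

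Third, mandatory completion is a deliberate choice, and freeing the whole sexual-health questionnaire from the lock could cost entire forms. This stands, and the remedy therefore keeps the lock.

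A reader might infer more than the documents support:

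- **That refusal deletes the t = 2 to t = 4 primary outcomes.** Separate submission from a login-only menu contradicts this.
- **That three of the five waves threaten the randomised comparison.** Only the t = 0 lock can reduce exposure during the 12 weeks.
- **That a refuser loses all help.** Public pages and contact with the community manager remain.
- **That the youngest, or those with negative experiences, refuse most.** This is plausible, but no figure in the article supports it.
- **That the plan contradicts its own decision not to ask about violence at entry.** That decision concerns registration, which is a different step from baseline measurement.

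**Conclusion.** The point holds as a badly fixed collection rule, limited in reach. As written, one refused item of a sensitive secondary questionnaire either shuts a participant out of the gated elements or invites an answer that cannot be recognised as untrue. The effect that matters most is at t = 0, through lack of exposure and possible exclusion under the five-visit rule. The next is at t = 2, through controls' delayed or missed access. Loss of primary data is indirect and depends on disengagement.

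The size cannot be derived from the documents; 5 to 10 of 100 participants per affected wave is an illustration that rests on an assumed 5% to 10%. The conclusion also assumes that the adapted items contain no decline response, which the article neither states nor rules out.

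**What to change.** Add an 'I would rather not answer' response to the items of the adapted Sex-under-25 questionnaire. Let it count as filled out for both submission and access, and code it as missing in the analysis. Present the IES and SCL-90-R first at each wave, so that they are submitted before the sensitive items appear. The access lock and forced completion of the primary scales can stay as they are. If the adapted questionnaire already offers such a response, one sentence saying so settles the point.

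The cost is a small change to the online form and some item-level missing data in a secondary outcome. The number of declined items would then be known and could be reported by group and age stratum.

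### The daily facts message puts text on family violence or sexual health on a participant's phone or in the mailbox, outside the login and the emergency exit: an avoidable disclosure risk of unknown size

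*Protocol article*

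**What the plan says.** The Intervention section of the protocol article describes the daily facts twice. Table 1 states that "participants receive a one-sentence fact of figure about family violence, sexual health, or reproductive health every day on their mobile or by e-mail", in a twelve-week cycle. The text below the table gives the purpose and route: "to stimulate participation, participants receive a fact or figure by email or text message every day". The restriction listed for this element is completion of the questionnaires; a login is not listed.

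The on-site Information element covers similar topics: "participants have access to tailored information about partner violence, sexual health, reproductive health, relations and healthcare". It requires a login as well as completed questionnaires. The emergency exit in the same table is described as "A button on every page directing participants to http://www.google.nl".

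On the population, Inclusion criteria says: "Any adolescent encountering family violence at home, whether this is direct or indirect, is considered to be exposed to family violence". The age range is 12 to 25. To explain why only the abused parent is asked for consent, Recruitment and informed consent says that "in cases of family violence, informing the abusive partner can be potentially dangerous".

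During the trial, "no changes will be made to the intervention, except for changes due to unexpected events", with bug fixes as the example.

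**The concern.** A message on a phone or in a mailbox can be seen by other people in the household. If it speaks of family violence, a reader at home may conclude that the adolescent is looking for help with it. Messages on sexual or reproductive health point that way less directly. The participants were recruited because of violence at home, and some are as young as 12.

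What is at stake is participant safety. The sample size, the analysis and the error rates are not affected.

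**Working it through.** No statistical formula applies and the plan has no figure to reproduce. The check sets the relevant parts of the protocol article side by side.

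1. **Content, frequency and route.** Table 1 fixes all three: one sentence on one of three sensitive topics, every day, by mobile or e-mail. The text below the table confirms e-mail or text message. The point therefore rests on a stated feature and not on a missing detail.

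2. **Reach of the login.** Information, Forum, Chat and Ask the expert all require a login in Table 1. Facts & Figures does not, because the message is sent out. Only participants who have already logged in and completed the questionnaires receive it, but once delivered it can be read without logging in.

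3. **Reach of the emergency exit.** It is a button on the site's pages. It cannot act on a text message or an e-mail.

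4. **Other stated protections.** Ethical and safety issues describes a username and password, a participant number, a secured server and moderation. These protect the site and the stored data, not a message already delivered. The contact with the community manager described there starts once a concern has arisen.

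5. **Foreseeability.** The inclusion criterion is exposure to violence at home. The Background notes that many mothers do not leave the abusive partner. The consent section treats an informed abuser as a possible danger. An abuser in the household is therefore foreseeable for some participants, although the article does not say for how many.

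6. **Who receives the messages, and how many.** The control group's restricted version of the site, as listed in the Intervention section, does not include the daily facts. In the first twelve weeks they reach the intervention group only; the control group receives them after gaining access. One cycle is 12 weeks × 7 days = 84 messages per participant. This counts messages and does not measure risk.

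7. **Size of the risk.** A probability of disclosure would need the chance that a message is seen, the share of participants living with the abuser, and the split of messages over the three topics. The article gives none of these, so no risk is computed.

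**The case against.** The strongest reply is that a journal article condenses the full protocol. Safe-contact rules, neutral wording or an opt-out may well be in documents not shown, such as the participant information letter, the site's pages on safety and privacy, or the community manager's protocol. This stands, so it cannot be said that the trial lacks such arrangements. What remains is the content and route that the article itself fixes.

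Several mitigations also stand. Participants register themselves by e-mail and hold their contact details in their own profile. Naming two routes may mean that they choose between them. They can reach the community manager and may stop. For those who needed parental consent, the consenting parent already knows. The inclusion criterion does not require that the participant lives with the abuser now, and the article gives neither the sender nor the exact wording of the messages. These facts lower the risk by an unknown amount. If the full sentence is sent, however, its topic remains in the message whichever route is chosen.

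A reader might infer three stronger points that the article does not support:

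- **That the plan contradicts itself.** The warning about the abusive partner is given to explain parental consent, and general information on family violence is open to any visitor to the site. An outgoing message about violence conflicts with neither statement. It differs from a public page only in that it is addressed to one person.
- **That the questionnaire reminders carry the same risk.** The article says "Participants receive a reminder in their personal menu and via a text message" but nothing about their content, so no finding can rest on them.
- **That the trial's results are affected.** Nothing in the outcomes, the comparison or the sample size depends on this feature.

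**Conclusion.** The point holds as a participant-safety matter in the design. The article sends sensitive text every day to a phone or mailbox, beyond the login and the emergency exit, in a population for whom it recognises the danger of disclosure. The risk is avoidable and its size is unknown.

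The conclusion assumes that the message carries the sentence as Table 1 describes it, and that at least some participants have someone at home who could see it and react badly. If unshown documents already provide a safe-channel choice, a neutral notice and an opt-out, the point reduces to confirming that. Because the cost is small and the freeze limits later changes to unexpected events, it should be settled before the trial starts.

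**What to change.** Before the intervention is frozen, add one setting to the existing user profile, with three choices:

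- the full sentence, by a channel the participant considers safe;
- a neutral notice, with a neutral sender and no wording on violence or sexual health, the fact itself being read after login;
- no messages.

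Leave the mood pop-ups and the five-visit rule in Data analysis unchanged. It may be tempting to exempt sessions opened only to read a fact. At login, however, the system cannot know which pages will be opened, and delaying the first pop-up would move the pre-session mood rating to after the fact has been read.

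The cost is one profile setting and one message template. Participants who choose the notice or opt out will see slightly fewer facts and have a weaker daily prompt to take part, which matters because the Discussion counts the daily facts among its measures against attrition. A neutral notice reduces the risk but does not remove it, since a daily message can still be noticed.
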